**Table 3. Primary and secondary outcomes and definitions.**

| Primary outcome measures     | Definition and calculation                                                                                                                                                                                                                                                                                                                                                                                                                                                                                                                                                                                                                                                                                                |
|------------------------------|---------------------------------------------------------------------------------------------------------------------------------------------------------------------------------------------------------------------------------------------------------------------------------------------------------------------------------------------------------------------------------------------------------------------------------------------------------------------------------------------------------------------------------------------------------------------------------------------------------------------------------------------------------------------------------------------------------------------------|
| FEASIBILITY           |                                                                                                                                                                                                                                                                                                                                                                                                                                                                                                                                                                                                                                                                                                                           |
| Feasibility                  | 
 
• Number of cancer clinical trials that meet study criteria and can be sampled
 
• Number of cancer disease types and studies that can be monitored for on Twitter simultaneously by the SC CTSI study team
 
• Characteristics of enrolled trials such as disease type, recruitment phase, clinical phase, target population and age
 
• Time and effort it takes the SC CTSI and USC Norris team members to respond to the resulting inquiries and decide whether or not to bring the patient in for screening
 
• Perspectives on clinically relevant increase in recruitment/Number of additional participants that studies can process
 
 |
| Eligibility rate of enrolled | Number of people eligible per month/Number of people screened per month (i.e.,                                                                                                                                                                                                                                                                                                                                                                                                                                                                                                                                                                                                                                            |

|                                      |                                                                                                                                                                                                                                                                                                                                                                                                                                                                                                                |
|--------------------------------------|----------------------------------------------------------------------------------------------------------------------------------------------------------------------------------------------------------------------------------------------------------------------------------------------------------------------------------------------------------------------------------------------------------------------------------------------------------------------------------------------------------------|
| trial participants                   | who spoke with the study team)                                                                                                                                                                                                                                                                                                                                                                                                                                                                                 |
| Diversity of enrolled participants   | Number of people of a specific racial/ethnic background enrolled per month/number of all people enrolled per month                                                                                                                                                                                                                                                                                                                                                                                             |
| Message click rate                   | Number of times a message link was clicked/Number of message impressions                                                                                                                                                                                                                                                                                                                                                                                                                                       |
| Website contact form usage rate      | Number of times a contact form was used on a trial webpage/Number of webpage sessions ( Sessions: Group of interactions a user takes on a webpage or website within a given time frame, e.g., page views, clicks. )                                                                                                                                                                                                                                                                                     |
| User acceptance and satisfaction (%) | 
 
• Number of USC Norris study team members who are satisfied with the SM monitoring and recruitment intervention/Number of all study team members engaged
 
• Number of PIs that are willing to participate (acceptance by PIs)
 
• Number of trial participants enrolled (Twitter users in LA County) who are satisfied with the SM monitoring and recruitment intervention/Number of all people engaged (i.e., who spoke with the study team)
 
 |
| IMPACT AND EFFICACY           |                                                                                                                                                                                                                                                                                                                                                                                                                                                                                                                |
| Enrolment rate per month             | 
 
• Number of people enrolled per month/Number of people contacted on Twitter per trial per month
 
• Number of people triaged and enrolled in another trial per month/Number of people contacted on Twitter per trial per month
 
                                                                                                                                                                                                                        |

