| Selection criteria                     | 
Inclusion criteria: Eligible clinical trials must focus on one or more of the pre-selected cancer disease types, i.e., non-small cell lung cancer, prostate cancer, breast cancer, colon cancer, kidney cancer, or lymphoma (trial selection is independent of stage of disease); be a Phase 1 trial in expansion, Phase 2, or 3; be interventional trials; recruit in English; be IRB-approved and open to accrual at USC Norris; recruit for at least 9 months at the point of enrollment; and set monthly accrual target <math>\geq 1</math>/annual accrual target <math>\geq 12</math>.
 
Exclusion criteria: Phase 1 trials in dose escalation.
                                                                                                                                                                                                                                                                                                                                                                                                                                                                                                                               |
| Investigational methods/Intended use   | 
 
1. We will use Sympplr Signals, a healthcare SM analytics platform that maintains a database of curated disease- and health-related Twitter conversations and user data, updated daily and easily sortable by SM user type (patient, physician, health care organization), location and time zone, language, disease/health interests, message content, sentiment, and SM influence. We will use the data to identify users on Twitter in LA County who mention specific disease/health-related keywords and contact them to recruit them into clinical trials. Those individuals are then targeted for recruitment using a combination of SM and traditional methods.
 
2. We will use semi-structured interviews to assess pre-and post-perspectives and concerns among PIs and research team members regarding the use SML and SM recruitment to recruit cancer trial participants.
 
3. We will use brief survey interviews to assess participant satisfaction with recruiting
 
                                                                                                                                                           |

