| Primary outcomes                                      | 1. Feasibility : Acceptance of and satisfaction with SM recruitment method among USC Norris study team members and Twitter users in LA County, number of cancer trials eligible to be enrolled in study, number of cancer disease types and studies that can be monitored for on Twitter simultaneously by the SC CTSI study team, time and effort it takes the SC CTSI and USC Norris team members to respond to the resulting inquiries and decide whether or not to bring the patient in for screening, eligibility rate of prospective participants, demographic and ethnic diversity rate of those who consented/enrolled, social media message click rate, website contact form usage rate.
2. Impact : Monthly observed recruitment rate vs. monthly projected accrual target by trial disease group compared to historic data. Effect size estimate of the number of people to enroll cancer trials as a result of targeted social media listening and recruitment (SML) via Twitter.                                                                                                                                                                                                                                                                                                                                                                                                                                                                                                                                                                                            |

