- Post-qualitative interviews with study team members will be undertaken to explore trial participants' views and experiences of the trial methods and intervention (principal investigators, clinical research coordinators, recruitment specialists). The interview guide is under development and will be submitted to the USC HSCIRB for review. Qualitative research expert [name] (consultant on this project) will advise this part of the study. We will gather a range of data. Please see **Table 3** that lists all outcomes in the *Data analysis* section 3.3.7.

Recruitment of USC Norris clinical trial team members: As we enroll cancer clinical trials in this study, the study co-PI ([name]) will contact the cancer trial PI via email (using USC's email system) to invite the PI and one additional study member (e.g., clinical research coordinator, recruitment specialist) to participate in an interview.

- Brief survey interviews with contacted Twitter users will be conducted by the study teams with prospective study participants who contacted the study team in response to SM recruitment. The goal of the survey is to collect demographic information about the prospective study participants and to better understand their perception of the SM recruitment method used. Qualitative research expert [name] (consultant on this project) will also advise this part of the study. (See **Appendix 6** for the full questionnaire)

Additionally, we will look at the impact of the SM intervention measured by monthly observed recruitment rate vs. monthly projected accrual target. We will calculate the effect size estimate of the number of people to enroll cancer trials as a result of targeted social media listening and recruitment (SML) via Twitter.

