**Figure 1. Study flow diagram of study design, procedures and stages for intervention A.**

## PARTICIPANTS

General characteristics of the proposed participant population(s): Any Twitter user who mentions one or more of the pre-selected cancer disease topics will be contacted via Twitter.

Anticipated number of research participants: We anticipate increasing the number of participants enrolled per trial and per month based on the following historic data from the past five years (see **Appendix 2**):

- Non-small cell lung cancer: Minimum of 2 participants per month
- Colon cancer: Minimum of 2 participants per month
- Prostate cancer: Minimum of 3 participants per month
- Breast cancer: Minimum of 2 participants per month
- Kidney cancer: Minimum of 1 participants per month
- Lymphoma: Minimum of 1 participants per month

Inclusion criteria for prospective trial participants: We will include all prospective trial participants in this study that come from Twitter in response of our SM recruitment interventions, provided they meet the specific trial's eligibility criteria.

Exclusion criteria for prospective trial participants: Persons who do not meet the eligibility criteria of any of the trials open to accrual will be excluded from participation, and persons who may be eligible (e.g., disease/histology, stage, prior treatment) but do not meet additional trial-specific requirements such as insurance or allergy to drug). These may vary by clinical trial. We will count these people as engaged but not enrolled and document the specific reasons.

Screening procedures: We will use the eligibility criteria as outlined above to verify clinical eligibility for participation in the study.

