### 2. Prospective participant data collection sheet

1. Name of prospective participant
  - a. First name
  - b. Last name

2. What's your Twitter handle?
  - a. \_\_\_\_\_
  - b. Prefer not to disclose
3. What's your email?
4. What's your birth date
5. Are you...?
  - Female
  - Male
  - Other
  - Prefer not to disclose
6. How do you describe yourself? (check all that apply)
  - African American / Black
  - American Indian / Alaska Native
  - Asian / Pacific Islander
  - Hispanic
  - Middle Eastern
  - White
  - Other
  - Prefer not to disclose
7. What is the highest degree or level of school you have completed?
  - No schooling completed
  - Nursery school to 8th grade
  - Some high school, no diploma
  - High school graduate, diploma or the equivalent (for example: GED)
  - Some college credit, no degree
  - Trade/technical/vocational training
  - Associate degree
  - Bachelor's degree
  - Master's degree
  - Professional degree
  - Doctorate degree
  - Prefer not to disclose
8. Did you respond to the social media recruitment message because you would like to learn more about a clinical trial?
  - a. Yes
  - b. No
9. Are you gathering information for yourself or on behalf of someone else?
  - a. For myself
  - b. On behalf of someone else

10. How helpful would you say is it when research institutions reach out directly to potential clinical trial participants via Twitter?
  - a. Very helpful
  - b. Helpful
  - c. Somewhat helpful
  - d. Not helpful at all
  - e. Don't know
11. How concerned are you about researchers and research institutions monitoring Twitter conversations to identify and contact potential study participants for clinical trials?
  - a. Very concerned
  - b. Somewhat concerned
  - c. Not too concerned
  - d. Not concerned at all
  - e. Don't know
12. When were you diagnosed with cancer?
13. Do you have active cancer? (Only if yes triage to USC Norris team)
  - a. Is it visible on scans (CT, MRI)?
  - b. Are you on active treatment?
14. Are you able to do activities of daily life independently? (e.g., eating, drinking, bathing)
15. Do you have a copy of your medical records?
16. Are you currently a patient at
  - a. USC Norris Comprehensive Cancer Center, or
  - b. USC Keck Medical Center, or
  - c. LA County USC?
17. Any other comments you want to share (free text)

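### The Twitter-user satisfaction percentage in Table 3 puts enrolled people over everyone engaged, so it cannot exceed the enrolment fraction, and no survey item asks about satisfaction

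*Protocol*

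**What the plan says.** The Synopsis opens its list of primary feasibility outcomes with "Acceptance of and satisfaction with SM recruitment method among USC Norris study team members and Twitter users in LA County". Table 3 in section 3.3.7 turns this into percentages under the row on user acceptance and satisfaction. For Twitter users the definition is "Number of trial participants enrolled (Twitter users in LA County) who are satisfied with the SM monitoring and recruitment intervention/Number of all people engaged", and engaged is explained as "i.e., who spoke with the study team".

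The staff measure in the same row is "Number of USC Norris study team members who are satisfied with the SM monitoring and recruitment intervention/Number of all study team members engaged".

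Section 3.3.3 (Participants) deals with people who fail the eligibility criteria or some further trial-specific requirement: "We will count these people as engaged but not enrolled and document the specific reasons".

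On measurement, the Synopsis states: "We will use brief survey interviews to assess participant satisfaction with recruiting" method. Section 3.3.1 says who is surveyed: "Brief survey interviews with contacted Twitter users will be conducted by the study teams with prospective study participants who contacted the study team". The questionnaire is given in full in Appendix 6. Its closest item to satisfaction, item 10, reads: "How helpful would you say is it when research institutions reach out directly to potential clinical trial participants via Twitter".

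**The concern.** A proportion satisfied should count satisfied people among those who could have been counted as satisfied. Here someone who spoke with the team, thought well of the approach and proved ineligible stays in the denominator but can never enter the numerator. The figure then depends on how many people qualify for and join a cancer trial, as well as on what users think of being contacted.

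The second part concerns the instrument. The survey is presented as the source of the satisfaction data, yet its items do not ask about satisfaction. Even the numerator cannot be counted from the questionnaire as it stands.

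Acceptance among Twitter users belongs to the first study objective, and Table 4 says that the feasibility data are meant to support a larger grant proposal. A percentage that cannot be read as satisfaction serves that purpose poorly.

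**Working it through.** The protocol states no target, sample size or expected value for this outcome, so there is no figure to reproduce. Two checks apply.

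**Check 1: the ratio.**

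Inputs:
- N = people engaged, that is, who spoke with the study team (Table 3).
- E = people enrolled in a trial. Section 3.3.3 makes this a different set from N, because some people are engaged but not enrolled.
- S = people who are both enrolled and satisfied (numerator in Table 3).

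Formula: S/N = (E/N) × (S/E).

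Because S cannot exceed E, S/N ≤ E/N. If every enrollee from Twitter spoke with the team, E/N is the enrolment fraction among engaged people, and the outcome cannot rise above it even if everyone is satisfied.

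The protocol gives no value for E/N. The table uses assumed values from 2% to 50%, and assumes the same satisfaction in enrolled and non-enrolled people. Example: 0.10 × 0.90 = 0.09.

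| Assumed E/N | Ceiling of the Table 3 ratio | Table 3 ratio if 60% satisfied | Table 3 ratio if 90% satisfied |
|---|---|---|---|
| 2% | 2% | 1.2% | 1.8% |
| 5% | 5% | 3% | 4.5% |
| 10% | 10% | 6% | 9% |
| 20% | 20% | 12% | 18% |
| 50% | 50% | 30% | 45% |

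A ratio with the same population above and below the line would read 60% or 90% in every row.

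The staff measure in the same row does use one population throughout: satisfied team members over team members engaged. The survey goes to prospective participants who contacted the team, not only to those who later enrol, so a matched numerator can be collected for Twitter users too.

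**Check 2: the instrument.**

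Appendix 6 has 17 numbered items:
- Items 1 to 7: identity and demographics.
- Items 8 and 9: why, and for whom, the person responded.
- Item 10: helpfulness of institutions' outreach on Twitter.
- Item 11: concern about monitoring of Twitter conversations.
- Items 12 to 16: disease status, function, records and current care.
- Item 17: free comments.

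Items that ask about satisfaction: none. Items 10 and 11 are related attitude questions, but both concern the practice in general rather than the respondent's own experience of being contacted. The data dictionary in Appendix 5 carries the same two attitude variables (value and concern) and no satisfaction variable. Nothing in the protocol links either variable to being satisfied.

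**The case against.** The strongest reply is that this is loose wording rather than an intended analysis. Table 3 also uses enrolled loosely in its eligibility-rate row, which is labelled for enrolled participants but defined as people eligible over people screened. The narrative statements of the outcome name Twitter users in LA County with no enrolment condition. The authors may well have meant all engaged users. That is plausible, but section 3.3.3 separates the two terms, and an analyst who follows the row as written would compute the wrong figure. The row still needs correcting.

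A second reply is that little depends on the number. This is a descriptive pilot, no threshold or test rests on this percentage, and nominal outcomes are to be presented as counts and percentages. The answers to items 10 and 11 can therefore be reported for all respondents whatever the ratio shows. This stands, and it limits the consequence: the attitude data are not lost.

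A third reply is that section 3.3.1 gives the survey's aim as understanding how users perceive the recruitment method, and that items 10, 11 and 17 do address perception and acceptance. This is fair for acceptance. It does not supply the satisfaction measure that the Synopsis and Table 3 name.

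A reader might also infer that a Don't know answer to item 10 or 11 would be scored as not satisfied. The protocol does not say so, since it maps no response to satisfied at all. How such answers are handled may properly be left to the statistical analysis plan.

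**Conclusion.** The Table 3 definition is wrong as written. It cannot exceed the enrolment fraction among engaged people, and it combines satisfaction with eligibility and enrolment. The bound follows from the definitions alone. Reading E/N as an enrolment fraction assumes that every enrollee from Twitter spoke with the team. The size of the distortion is unknown, because the protocol gives no enrolment fraction, and the percentages tabulated above are illustrations only. Separately, the survey said to assess satisfaction contains no satisfaction item.

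Two stronger readings are tempting and are not supported. One is that the result would show users rejecting the method: the protocol sets no threshold, and the answers on helpfulness and concern can be reported alongside. The other is that the ratio measures enrolment instead of satisfaction: it is the product of the two. The point is a correction to the definition of one primary outcome and its instrument, not a flaw in the study design.

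**What to change.** Reword the Table 3 entry so that both parts refer to the same people: engaged Twitter users who are satisfied, over engaged Twitter users who answered the item. Show enrolled and not enrolled users separately beneath the overall figure.

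Then settle what is measured, in one of two ways:
- add one closed satisfaction item to Appendix 6, with a matching variable in Appendix 5; or
- name items 10 and 11 as the acceptance measures, align the wording of the Synopsis and Table 3 with that, and report the full response distribution of each item, including Don't know. This avoids having to choose a cut-off.

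The cost is one reworded row and at most one extra survey question. The group to be surveyed does not change.
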